## Abstract

**Background:**

People who use drugs (PWUD) are at high risk for hepatitis C virus (HCV) infection and its complications. Given the high prevalence rate of HCV in PWUD, the World Health Organization (WHO) emphasizes PWUD as a target population for HCV elimination. The introduction of pangenotypic direct acting antivirals (DAAs) greatly simplifies HCV treatment, which encourages integration of HCV treatment in primary care. Facilitating low threshold HCV care for PWUD by implementing decentralized models is crucial for HCV elimination.

**Aims:**

With this study we aim to (1) eliminate 90% of identified HCV infections in Dutch addiction care, using a decentralized PWUD-HCV care model, and (2) identify facilitators and barriers for successful implementation of the model using interviews.

**Methods:**

We will perform a multicenter mixed-method study on HCV treatment in addiction care. In a prospective observational study we will examine HCV-related outcomes in PWUD receiving HCV treatment as part of addiction care. The primary outcome is viral elimination, defined as percentage of identified HCV positive patients cured with DAAs. In parallel, we will perform a qualitative study to explore facilitators and barriers for implementation of fully decentralized HCV-PWUD care. We will interview addiction care professionals and board members about their experience with HCV-care as part of addiction care.

**Discussion:**

This study will show effectiveness of integration of HCV care within addiction care, and provide insight in facilitators and barriers to implement integrated HCV-addiction care. The results will provide recommendations for implementation and maintenance of the decentralized HCV pathway, which can facilitate scaling-up to contribute to reaching WHO HCV elimination goals.

*Trial registration* NCT05401136.

## Background

The World Health Organization has set ambitious goals to eliminate hepatitis C virus (HCV) as a public health threat, aiming at a 90% reduction of new HCV infections and a 65% reduction of HCV related mortality [1, 2]. Disease progression models indicate only 24% of high-income countries are on track for achieving these goals before 2030 at the current rate of diagnosis and treatment [3, 4]. Expansion of efforts is therefore required.

One paramount strategy to reach HCV elimination goals is micro-elimination in specific target populations where HCV is prevalent, such as people who use drugs (PWUD). An estimated ~ 3,400 HCV RNA positive former and current injecting drug users remain in the Netherlands, despite availability of free HCV care across the country [5]. Injecting drug users are a subpopulation of PWUD and prevalence in the total Dutch PWUD population is currently unknown.

Studies indicate that HCV-infected PWUD may frequently get lost in the HCV care chain from diagnosis, to initiation of treatment and follow-up [6]. Recent studies showed that a median of 50% of PWUD with HCV visit the HCV specialist after testing positive and subsequently only 53% of those initiate treatment [7]. Loss to follow up during (median 2.5%) and after treatment (median 7.1%) were comparable to the general population [7]. Between 2013 and 2016 the Dutch HCV standard of care in addiction centers was evaluated and improved. Although major strides were made, linkage to hospital care and treatment remained as significant barriers due to DAA restrictions [8].

Over the past decade, DAA therapy became widely available and is now standard care globally. Recently, the use of pangenotypic DAAs, which bypass genotyping and simplify therapy choice, were recommended by both American Association for the Study of Liver Diseases (AASLD) and European Association for the Study of the Liver (EASL) [9, 10]. Furthermore, evaluation of liver fibrosis can be done using non-invasive, inexpensive and reliable biomarker panels, further reducing complexity of HCV care and burden for patients [10]. As a result, initiatives to offer decentralized HCV care for PWUD have been studied. A recent meta-analysis showed increasing linkage to care, with increasing levels of decentralization [11]. With full decentralization, HCV testing and treatment at the same site, showed the highest linkage to care of 72%, whereas without decentralization this was only 47%. Treatment uptake rate showed similar results [11]. Successful implementation of decentralized pathways are therefore the next step in achieving HCV elimination in PWUD [12, 13].

Previous studies have examined challenges in implementation of HCV care for PWUD outside of the hospital care setting [14–17]. Linkage to HCV care in PWUD may be reduced as a result of poor venous access due to damaging effects of intravenous drug use which precludes laboratory monitoring of treatment. A recent qualitative telephone interview study in general practitioners who prescribe opioid agonist therapy and addiction care specialists also identified logistic barriers like lack of testing on-site, and difficulty in liver fibrosis assessment [18]. There remains a need for addiction care focused research emphasizing residual local barriers, for instance stigmatization and lack of support for task shifting at management level. Nurses also play a vital role in addiction care, their perspectives are lacking in literature.

Dutch addiction care is provided through an integrated trajectory and joins government, municipality, justice system and health service providers with common goals of public order as well as public health and quality of care and treatment. Addiction care centers are a part of mental healthcare and deliver care that targets specific populations, provide outreach, night shelters, outpatient- and inpatient addiction treatment facilities. In addition, these institutions provide and coordinate reintegration projects, daytime activities, education and harm reduction (i.e. needle exchange programs) [19].

We aim to evaluate the effectiveness and feasibility of the HCV: Chain of Addiction Care project, which decentralizes HCV care in Dutch addiction care. This mixed-method study consists of (1) an observational study to explore its effectiveness in achieving 90% hepatitis C elimination, and (2) a qualitative study to explore facilitators and barriers for its implementation.

## Methods

### Study design

This mixed-method study consists of two parts. Part 1 is a multi-center observational cohort study that will study the effectiveness of the structured implementation of CAC in a PWUD population receiving addiction care. Part 2 is a qualitative study using semi-structured interviews regarding addiction care professionals’ personal perspective on barriers and facilitators for implementation of the CAC pathway. We will focus on addiction care specialists and nurses, as well as board members in addiction care as all play a vital role in successful implementation of decentralization projects. The interviews will either take place face-to-face or digitally using a videoconferencing platform. The interviews will be audio recorded and transcribed verbatim. The mixed-method design will be integrated into the RE-AIM framework to allow for evaluation using a well-established method for implementing community-based health interventions. The RE-AIM framework facilitates the translation of research to practice with attention for contextual factors, as opposed to only efficacy or effectiveness [20]. RE-AIM involves evaluation in five dimensions (Reach, Effectiveness, Adoption, Implementation, Maintenance), resulting in a more explicit description of the strategy. RE-AIM has been used extensively in over 450 publications on study planning or intervention evaluation [21].

### The chain of addiction care (CAC) project

The CAC pathway is a new approach to HCV care in the Dutch addiction care setting, in line with regular HCV care guidelines [9, 10]. All five addiction care organizations in the Nijmegen Institute for Scientist-Practitioners in Addiction (NISPA) collaboration will be invited to participate but we will also reach out to other major addiction care organizations to achieve nationwide coverage. All centers will be invited within a timeframe of two months. There will be no financial compensation for participation, however participation will include free education on hepatitis C. We anticipate that at least four out of five NISPA organizations and at least two non-NISPA organizations will participate. We will focus on centers that provide outpatient care, outreaching care or methadone posts, as these settings will contain most patients at risk for bloodborne infections and be suitable to provide hepatitis C care. Unfortunately, inpatient hepatitis C treatment is not currently reimbursed in the Netherlands. All phases of HCV care tasks are shifted to the addiction care physicians (ACP) and nurses, from case finding in patients with a risk for bloodborne infections to counselling, testing, treatment and follow-up. Patients at risk who visit the participating centers will be educated on viral hepatitis and HIV and motivated to undergo venipuncture. In the majority of patients, pangenotypic DAA treatment will be provided by the ACP after evaluation of biomarker panels (Fig. 1).

**Fig. 1 Fig1:**
[figure not shown]
*CAC flowchart* *decompensated cirrhosis as indicated by FIB-4 score (> 3.25) and Child–Pugh score B or C; compensated cirrhosis as indicated by FIB-4 score (> 3.25) and Child–Pugh score A

CAC is a project that is part of the portfolio that is offered by HepNed, a collaboration between hepatologists and infectious disease physicians. HepNed coordinated the nationwide hepatitis C retrieval program CELINE [22]. During the CAC project, as addiction care teams are familiarized with HCV care, a HepNed expert is available for advice and instruction. In some cases treatment provided by a viral hepatitis expert is preferred: in patients with co-infection hepatitis B or HIV, renal impairment (eGFR < 30 ml/min/1.73m^2^) and in patients who previously failed DAA therapy or patients who present with decompensated cirrhosis (Child–Pugh B and C). In case of advanced fibrosis or compensated cirrhosis (Fib-4 > 3,25 and Child–Pugh A), patients receive hepatitis C treatment in addiction care and are simultaneously referred for fibrosis analysis and cirrhosis follow-up in secondary care. Patients who fail treatment will be referred to specialist care. After completing the treatment, patients will be counselled and reintroduced into established health screening programs. Patients with an HCV reinfection will be treated as new patients and can be treated on-site again.

Implementation requires a dynamic and tailored approach to the local situation in the individual addiction care center based on variation in availability of on-site venipuncture, outreaching healthcare providers and existing collaborations with viral hepatitis experts. Derived from barriers found in previous studies, CAC interventions include DAA provision in methadone distribution posts and a limit to excess blood withdrawals by testing in combination with health screenings and implementation of reflex HCV-RNA testing.

### Study population

In Part 1 addiction care physicians will invite consecutive people who inject(ed) drugs or have other risk factors for HCV infection and who visit the CAC addiction care centers to participate. In order to be eligible for this study, a subject must be aged 18 years or older and able and willing to give informed consent. For the duration of the project, as many patients as possible will be included. There are no exclusion criteria for this study. Patients will be followed-up until the end of their HCV care journey. Since the CAC pathway is standard care in a decentralized setting, no comparison group can be formed. In part 2 we will invite addiction care physicians, nurses and addiction care policy makers employed both in centers participating in CAC and centers who do not.

### Study outcomes

The primary outcome in part 1 is HCV viral elimination, defined as percentage of patients that achieved SVR among identified HCV RNA positive patients. Secondary outcomes are total number of patients tested, prevalence of HCV antibody and RNA positivity among tested patients, fibrosis stage in HCV positive patients as found by FIB-4 and/or Child–Pugh scores, decentralized treatment initiation rate, treatment completion, sustained virologic response rate and referral. The main study outcomes for part 2 are the barriers and facilitators contributing to (un)successful implementation of the HCV care pathway for PWUD in the Netherlands.

### Data collection and management

The main study parameters collected are: acceptance rate of (on-site) testing, HCV prevalence, treatment acceptance rate, sustained virologic response (SVR) rates and re-infection rates. Furthermore, we will collect data on patient characteristics such as sex, age, history of drug use, medical history and comorbidities (including previous HCV infection and treatment), concomitant medication and available HCV-related clinical data (e.g. other risk factors, blood test results, liver fibrosis stage). All these parameters are stored in the electronic patient files by the patient’s treatment team as part of standard care. Data will then be collected anonymously by a member of the research staff according to the medical code of conduct [23]. A validated and GCP compliant data management program, CastorEDC, will be used for central data storage.

Interview recordings in part 2 of the study will be anonymized and used solely by the researches. The interview guide will address the following topics: preferred role of addiction center in HCV care: specifically for diagnosis, treatment and follow-up; experience and viewpoint on fully decentralized HCV care; real and anticipated barriers and facilitators for successful and sustainable implementation. Interviewee data collected includes participant characteristics such as sex, age, occupation and years of experience.

### Analysis

For the quantative study (part 1) we will use descriptive statistics. Primary and secondary endpoints, as well as baseline patient characteristics will be presented as percentages, means (± SD) or medians (IQR), depending on the variable and its distribution. No sample size is recorded as this is an observational prospective cohort study without a comparison group. All analyses will be performed using the statistical package SPSS, version 25.0 (SPSS Inc. Chicago, IL, USA).

In the qualitative study (part 2), Braun and Clarke’s approach to thematic analysis will be used to identify common themes across the interview transcripts [24]. The analysis will involve a six-phase process: familiarization with the transcripts, coding, searching for themes, reviewing themes, defining and naming themes and writing. The coding process will be data driven, in which codification is performed following an inductive method and themes are constructed from the data. Each transcript will be coded in pairs of 2 researchers. Qualitative thematic analysis will be performed using ATLAS.ti v9.1.6.

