## Discussion

HCV viral elimination in line with WHO goals is within reach [4]. Micro-elimination efforts in target populations like PWUD are essential in countries with a low HCV prevalence in the general population like the Netherlands. This study aims to test a decentralization model tailored to population and system needs, aimed to integrate HCV care within addiction care, with the specific objectives to (1) test effectiveness in achieving 90% elimination viral elimination rates; and (2) explore facilitators and barriers for implementation of decentralized HCV care within addiction care.

Efficient, low-threshold treatment for HCV-infected PWUD is one strategy of HCV-micro-elimination to reduce the human reservoir of HCV and contribute to HCV elimination goals of the WHO [25]. The findings of this study will strengthen the evidence base for decentralized HCV-care within addiction care. Furthermore, identification of facilitators and barriers for implementation of a decentralized HCV-care model within addiction care can identify best practices and feed into a blueprint to support scaling-up of HCV care decentralization. Thus, the current study will contribute to achieving WHO HCV elimination goals.

We make use of the RE-AIM framework to systematically evaluate all necessary dimensions for successful implementation of decentralized HCV care. It has to be acknowledged that commonly not all dimensions of the RE-AIM framework are covered within a single study. This also applies to the current study, where research objective one provides information on both reach and effectiveness of the intervention in real life, and the qualitative research objective two will mainly provide information on implementation (see Table 1). If successful, future studies should explore maintenance of decentralized HCV care within addiction care.

**Table 1 Tab1:** Methods and endpoints in the RE-AIM framework

Quantative study endpoints: HCV care pathway (part 1)	RE-AIM dimension^a^	Qualitative study endpoints: barriers and facilitators (part 2)
• Demographics of population • Proportion of population tested	*Reach*	• Individual reasons for not participating • Recruitment of patients • Willingness to participate
• Viral elimination rate	*Effectiveness*	**–**
• Proportion of centers participating	*Adoption*	• Willingness to initiate the program

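### The study says it tests whether 90% elimination is achieved and means to carry the answer elsewhere, but the stated primary analysis is a percentage without an interval

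*Protocol article*

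**What the plan says.** The 90% figure is worded in three ways in the protocol article:

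- The abstract's Aims set a target: to "eliminate 90% of identified HCV infections in Dutch addiction care, using a decentralized PWUD-HCV care model".
- The Background describes "an observational study to explore its effectiveness in achieving 90% hepatitis C elimination".
- The Discussion states the objective as to "test effectiveness in achieving 90% elimination viral elimination rates".

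Under Study outcomes, the primary outcome is one proportion, "defined as percentage of patients that achieved SVR among identified HCV RNA positive patients". Study population says that no comparison group can be formed and that enrolment is open-ended. The 90% value is therefore the only reference for effectiveness.

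The Analysis section is explicit about the method: "For the quantative study (part 1) we will use descriptive statistics". Endpoints "will be presented as percentages, means (± SD) or medians (IQR), depending on the variable and its distribution". It adds: "No sample size is recorded as this is an observational prospective cohort study without a comparison group".

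Among the strengths listed in the Discussion is that findings can be transferred to other addiction care facilities in the Netherlands and abroad.

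**The concern.** An aim framed as testing a fixed value, and meant to inform settings outside the cohort, needs a statement of how far the observed proportion could lie from the underlying one. The analysis as written supplies only the observed proportion. The article does not simply leave the method open: it names the method for the primary endpoint, and that method is descriptive.

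The reason given for having no sample size adds to the problem. Lack of a comparison group does not remove sampling error from a single proportion, and its precision can be calculated for any assumed number of patients.

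At stake is the headline result. A figure close to 90%, printed alone, could be taken as showing that the care model delivers 90% elimination, when the same data may be compatible with rates well below that.

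**Working it through.** **Inputs.** The benchmark is 90% (Aims, Background, Discussion). The outcome is SVR divided by identified HCV RNA positive patients (Study outcomes). The number of such patients is not given, so n = 50, 100, 200 and 400 are assumptions. The article states no interval, power or sample size, so there is no figure of its own to reproduce.

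**1. Interval at an observed 90%.** The Wilson 95% limits are [p + z²/(2n) ± z√(p(1−p)/n + z²/(4n²))] / (1 + z²/n), with p = 0.90 and z = 1.96. For n = 100, the centre is (0.90 + 0.0192)/1.0384 = 0.885 and the half-width is 0.060, which gives 0.826 to 0.945.

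| Assumed n | Cured | Wilson 95% | Exact 95% |
|---|---|---|---|
| 50 | 45 | 78.6-95.7% | 78.2-96.7% |
| 100 | 90 | 82.6-94.5% | 82.4-95.1% |
| 200 | 180 | 85.1-93.4% | 85.0-93.8% |
| 400 | 360 | 86.7-92.6% | 86.6-92.8% |

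Unrounded, the Wilson upper limit at n = 100 is 94.48%, so it rounds to 94%.

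**2. What a bare percentage would do if read as 90% or more means achieved.** The article states no such rule; this only shows the sampling error. The exact binomial P(X ≥ 0.9n) at a true rate of 85% is 21.9% (n = 50), 9.9% (n = 100) and 2.5% (n = 200). In the other direction, at a true rate of 93% the observed figure falls below 90% with probability 13.5% (n = 50), 9.1% (n = 100) and 4.2% (n = 200).

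**3. Precision without a comparison group.** n = 1.96² × 0.9 × 0.1 / h² gives 35 HCV RNA positive patients for a half-width h of 10 points, 139 for 5 points and 385 for 3 points.

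**4. Clustering, as an illustration only.** The article expects at least four plus two, so at least six, organizations, with a pathway adapted to each. With n = 100 in six equal groups, the design effect is 1 + (100/6 − 1) × ICC. The article gives no ICC. An assumed 0.01, 0.05 or 0.10 gives design effects of 1.16, 1.78 and 2.57, effective n of 86, 56 and 39, and Wilson intervals of 82-95%, 79-95% and 77-96%. The size of this effect depends wholly on the assumed ICC.

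**5. What a strict rule would cost.** If success required a lower 95% limit of at least 90%, the counts needed would be 50/50, 96/100 or 189/200. At a true rate of 93% these are reached with probability 3%, 16% and 25%.

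**The case against.** The strongest reply is that, for one reading of the aim, the percentage is the answer. The Aims set a target for identified infections, and the outcome uses identified HCV RNA positive patients. If the question is only whether 90% of these patients were cured, a count settles it. This stands, and it limits the point to the objective as worded in the Discussion and to the transfer of results to other settings.

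Three stronger readings are tempting, and the article does not support them:

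- A reader might infer that the whole article promises a test of 90%. Only the Discussion uses that verb for the 90% aim. The Background speaks of exploring, and the Aims state a target.
- A reader might infer that the study will declare its aim met or missed on the point estimate. No such rule appears anywhere.
- A reader might infer that ignoring centres invalidates the analysis. The article is silent on centre-level reporting, which a condensed article may leave to a fuller document, and no ICC is available to size the effect.

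It is also fair to say that the sample-size sentence contains no miscalculated figure. HCV prevalence in the total Dutch PWUD population is described as unknown, so any planned number would have been uncertain. The sentence is a weak justification rather than a numerical error. Finally, if numerator and denominator are published, a reader can compute a simple interval. That lowers the severity, but it does not excuse a plan that leaves the interval out.

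**Conclusion.** The point holds in limited form and should be fixed, though it is not critical. The stated analysis is adequate for describing the cohort. It is not adequate for the objective of testing effectiveness against 90%, or for applying the result elsewhere. At modest numbers the gap matters: an observed 90% is compatible with about 79-96% at n = 50 and 83-94% at n = 100, narrowing to 87-93% at n = 400. These intervals assume the stated n and independent patients; clustering by centre would be expected to widen them by an unknown amount. A requirement that the lower limit reach 90% does not follow from this. It would replace achieving 90% with demonstrating more than 90%, and it would usually fail at the smaller sizes even when the true rate is 93%.

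**What to change.** - In the Analysis section, state that the primary proportion will be reported with numerator, denominator and a two-sided 95% Wilson or exact confidence interval, and interpreted against 90% as an estimate with its uncertainty.
- Align the objective in the Background and Discussion with estimation, for example: to estimate the elimination rate and describe it relative to the 90% target. The target in the Aims can stay.
- Add centre-level percentages as a descriptive supplement, and an interval that allows for clustering as a sensitivity analysis. With about six organizations, between-centre variance will be poorly estimated, so this should not be the main result.
- Replace the sentence that ties the absent sample size to the absent comparison group with one saying that enrolment is open-ended and that precision will be shown by the interval.
- A strict rule on the lower limit is optional. If one is wanted, it should be stated in advance with its chance of being met.

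The cost is a few sentences and a little programming. No extra patients or data are needed and care does not change. The downside is that the reported result becomes less definite than a single percentage.
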